# Effect of voluntary breathing exercises on stable coronary artery disease in heart rate variability and rate-pressure product: a study protocol for a single-blind, prospective, randomized controlled trial

**DOI:** 10.1186/s13063-020-04402-2

**Published:** 2020-07-01

**Keywords:** Breathing, Stable coronary artery disease, Heart rate variability, Blood pressure, Myocardial oxygen consumption

## Abstract

**Background:**

At present, China has more than 11 million patients with stable coronary heart disease and this is becoming a major public health problem. The pathological changes of coronary heart disease can lead to dysfunction of the cardiac autonomic nervous system, which increases the risk of complications such as malignant arrhythmia (ventricular flutter, ventricular fibrillation, etc.), heart rate, systolic blood pressure, and rate-pressure product (RPP), which is highly correlated with myocardial oxygen consumption and indirectly reflects myocardial blood supply and oxygen consumption. Although the guidelines recommend that such patients take drugs to reduce heart rate and myocardial oxygen consumption, the clinical control of heart rate is still not ideal. Thus, in this trial, we will use voluntary breathing exercises as the strategy of exercise rehabilitation for patients with stable coronary artery disease (SCAD), in order to increase the vagus nerve activity and/or reduce the sympathetic nervous activity, help maintain or rebuild the balance of plant nerve system, improve the time-domain index of heart rate variability, reduce the burden on the heart, and relieve patients’ anxiety and other negative emotions.

**Methods:**

This is a 6-month single-blind, randomized controlled clinical trial that will be conducted in the First Affiliated Hospital of Soochow University. A total of 140 patients who fill out the Informed Consent Form are registered and randomized 1:1 into the Voluntary Breathing Exercises (VBE)-based clinical trial monitoring group (n = 70) or the Routine follow-up group (n = 70). The VBE-based clinical trial monitoring group is given VBE training on the basis of conventional treatment and health education, while the control group received conventional health education and follow-up. The primary outcomes will be measured heart rate variability and RPP. Secondary outcomes will include changes in Self-rating Anxiety Scale, total cholesterol, triglyceride, high-density lipoprotein, low-density lipoprotein, weight, and body mass index.

**Discussion:**

This trial will carry out scientific respiratory exercise for patients with SCAD, which belongs to the category of active secondary prevention for patients, and changes from remedial to pre-protective. VBE is easy to operate and is not limited by time and place. It is important and meaningful to carry out VBE for patients with SCAD. This study will provide considerable evidence for further large-scale trials and alternative strategies for the rehabilitation nursing of patients with SCAD.

**Trial registration:**

Chinese Clinical Trials Registry, 1900024043. Registered on 23 June 2019.

## Background

Stable coronary artery disease (SCAD) is one of the most common types of coronary artery disease. It is characterized by chronic delay and high recurrence. Several studies [1–3] have demonstrated that pathological changes of coronary heart disease can lead to dysfunction of the cardiac autonomic nervous system, which is manifested as hyperactivity of sympathetic nerve and decreased excitability of vagus nerve. Thayer et al. [4] concluded that autonomic nervous dysfunction leads to cardiac dysfunction and cardiovascular disease. Patients are also at an increased risk of complications such as malignant arrhythmia (ventricular flutter, ventricular fibrillation, etc.), increased heart rate, increased systolic blood pressure, and increased rate-pressure product (RPP), which is highly correlated with myocardial oxygen consumption and indirectly reflects myocardial blood supply and oxygen consumption [5], and is earlier than the change of electrocardiography (ECG). RPP is the product of heart rate and systolic blood pressure and has been used as a non-invasive indicator to assess the level of myocardial oxygen consumption since the 1970s. The basis of the common pathophysiology of the risk complications such as angina pectoris and acute coronary events is myocardial ischemia and hypoxia. RPP is closely related to myocardial oxygen consumption (*R* = 0.90) [6], which is not only used to formulate the amount of exercise prescribed, but also the basis for evaluating the symptoms and exercise ability of patients with cardiovascular disease. To some extent, it reflects the tolerance and safety of certain rehabilitation methods of cardiovascular patients. As a consequence, it is of utmost importance to no longer neglect the stability of autonomic nervous function during rehabilitation of SCAD. Heart rate variability (HRV) is recognized as a new non-invasive quantitative evaluation method of autonomic nervous system function developed in recent years [7]. HRV refers to the small difference between cardiac cycles, which reflects the sympathetic and vagus nervous systems regulating the balance state of the cardiovascular system [8]. It was shown to be related to subtle time changes and patterns of each cardiac cycle, while the average heart rate can only appear normal or abnormal. Shen et al. [9] analyzed the results of 24-h dynamic electrocardiogram of 156 patients with coronary heart disease and found that HRV decreased, ejection fraction decreased, and the incidence of cardiovascular events increased.

The research on the effect of respiration on HRV has become a hot topic in recent years [10, 11]. Previous studies have demonstrated that respiration is one of important influencing factors for HRV [12, 13]. Cicek et al. [14] confirmed that deep and slow breathing can make people turn from depression to relaxation and improve the regulation function of human organs or autonomic nerves, so as to improve the adaptability of human body. Voluntary breathing exercises (VBE) refers to a treatment or method of rehabilitation for adjusting breathing behaviors by trainees according to certain breathing patterns (frequency, depth, ratio of expiratory/inspiratory time, chest/belly style) without the use of auxiliary equipment or equipment [15]. Initially, VBE was applied in the prevention and treatment of chronic obstructive pulmonary disease [16], chest surgery [17], and other diseases related to respiratory system. Subsequently, it gradually spread to the treatment of other chronic diseases such as the endocrine and nervous systems [18, 19]. Some authors consider that VBE effectively improved quality of life, reducing symptoms associated with a variety of anxiety and depression [20, 21]. VBE is also applied to treat cardiovascular complaints, such as primary hypertension [11, 16], heart failure [19, 22, 23], arrhythmia [24], and so on. Kawecka-Jaszcz et al. [23] found that respiratory exercise combined with exercise rehabilitation for a period of 10–12 week in patients with chronic heart failure had a better effect on ejection fraction and 6-min walk test, but this study failed to observe the functional changes of autonomic nervous function. Westerdahl et al. [25] showed that respiratory exercise for 2 weeks reduced systolic blood pressure in patients with coronary heart disease, but had no effect on heart rate and diastolic blood pressure, which may be closely related to the short intervention time. A study on the efficacy of VBE by Huang et al. [26] also reported significant reductions in heart rate and systolic blood pressure, and there were no effects on diastolic blood pressure. The meta-analysis of results of independent breathing exercise conducted by the research team in the previous stage proved this [27] (six randomized controlled trial [RCT] articles, all in English), VBE had significant effects on improving resting heart rate, systolic blood pressure, and diastolic blood pressure in patients with coronary heart disease.

However, more research is necessary regarding the effect of VBE on SCAD. In 2014, the American College of Cardiology (ACC) and the American Heart Association (AHA) [28] pointed out that drug therapy and lifestyle intervention are key to controlling or delaying the stable progression of coronary heart disease, reducing complications, disability rate, and mortality rate. As a lifestyle intervention, VBE has become a new way of comprehensive intervention for coronary heart disease. To date, there are no definite data on the effect of VBE in patients with SCAD, particularly in the Chinese population. Thus, we present the protocol of a single-blind RCT to investigate the effects of VBE on SCAD. We hypothesize that VBE is effective for the management of secondary prevention of coronary heart disease.

### Research hypothesis

On the basis of routine rehabilitation guidance, in this study VBE will act as an aid in the strategy of exercise rehabilitation in patients with SCAD, in order to increase activity in the vagus nerve and/or reduce sympathetic nervous activity, help maintain or rebuild the balance of the central nervous system, improve the time-domain index of HRV in patients with SCAD, reduce the burden on the heart, and relieve patients’ anxiety and other negative emotions (Fig. 1).

**Fig. 1 Fig1:**
[figure not shown]
Schematic diagram of research hypothesis

### Objectives

The main goal of this RCT is to evaluate the effect of VBE on HRV and myocardial oxygen consumption in patients with SCAD. First, HRV will be measured using the generally recommended time-domain analysis in 24 h; second, since RPP are highly correlated with myocardial oxygen consumption, it will be used as an indicator to estimate oxygen consumption of the myocardium.

The second objective is to explore the effect of VBE on reducing anxiety in patients with SCAD. Anxiety will be measured using the Self-rating Anxiety Scale (SAS) developed by Zung [29] in 1971.

## Methods

### Study design and setting

This is a 6-month, single-blind RCT that will be conducted in the First Affiliated Hospital of Soochow University. Written informed consent will be obtained from each individual by the researcher after the individual has received a sufficient explanation and period of time in which to make a thoughtful decision. All the patients will be randomized 1:1 into the VBE-based clinical trial monitoring group (n = 70) or the Routine follow-up group (n = 70). The VBE-based clinical trial monitoring group is given VBE training on the basis of conventional treatment and health education, while the control group received conventional health education and follow-up. The two groups will be followed up for 3 months (Step 1). Considering the ethics and the fairness of the resources, we refer to the step-wedge design [30] and give the control group the same VBE guidance and follow up for another 3 months (Step 2) (see the flow diagram in Fig. 2). The Cardiovascular Medicine Department of the First Affiliated Hospital of Soochow University is currently the largest cardiovascular disease diagnosis and treatment center in South Jiangsu Province, China. The department carried out the first PTCA surgery in China in 1983. It has 180 beds, including 20 fully equipped Coronary Care Unit (CCU) beds, four cardiac catheterization rooms with advanced equipment, as well as a cardiac supersonic room and cardiac function room, and 1500 m^2^ cardiovascular laboratory. Annually, an average of 100,000 outpatients, 5000 open-heart surgery candidates, and 400 emergency operations are treated in the department.

**Fig. 2 Fig2:**
[figure not shown]
Technology roadmap

### Sample size

The sample size estimation was carried out using G Power 3.1.9.2 software of two population means formulae [31]. We hypothesized that the VBE-based clinical trial monitoring group would be superior to the control group in terms of HRV and myocardial oxygen consumption; the effect rates were calculated with a 0.447 effect size at a 5% significance level and a power of 0.8. This means a sample size of 118 individuals per group was required. With an estimated 20% dropout, the final sample size of 140 individuals was determined (70 in each group).

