### Randomization

Eligible participants who will provide written consent to participate in this clinical trial will be randomly assigned to a treatment group or a control group with an allocation ratio of 1:1. Random sequencing will be generated by an independent professional statistician using the EXCEL to generate 140 random numbers. The serial numbers assigned to each patient are kept in an opaque, sealed envelope. All the participants will be asked to pick one sealed envelope and pass it onto the research study team member. The participants will be randomly assigned to two groups. Each group will have 70 individuals.

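### The sample size paragraph contradicts itself, 118 does not follow from its inputs, and 140 randomised with 20% dropout gives about 65% power two-sided (76% one-sided), not 80%

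*Protocol article*

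**What the plan says.** All of the calculation is in Methods, Sample size. The method: "The sample size estimation was carried out using G Power 3.1.9.2 software of two population means formulae". The inputs: "the effect rates were calculated with a 0.447 effect size at a 5% significance level and a power of 0.8". The result: "This means a sample size of 118 individuals per group was required". The dropout step: "With an estimated 20% dropout, the final sample size of 140 individuals was determined (70 in each group".

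The design number is the same everywhere else. The Abstract and Study design and setting give 70 per group, and Randomization has 1:1 allocation and says "Each group will have 70 individuals". Blinding also refers to 140 participants.

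The paragraph does not say whether the test is one- or two-sided. It expects the intervention group "would be superior to the control group in terms of HRV and myocardial oxygen consumption", and Statistical analysis gives only a significance threshold of P < 0.05. It also does not say which measure the single effect size refers to, although Primary outcome measure names both HRV (five time-domain indices) and RPP.

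**The concern.** The number required before dropout (118 per group) is larger than the number enrolled after allowing for dropout (70 per group). That order is impossible, so at least one figure is wrong, and a reader cannot tell which.

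What is at stake is the claim of 80% power. If 140 randomised does not deliver it at an effect of 0.447, the trial is more likely to miss its own target effect than it says. A non-significant result could then be given more weight against the breathing exercises than the design supports.

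**Working it through.** **Inputs** (all from Sample size, except allocation, which is from Randomization): d = 0.447, alpha = 0.05, power = 0.80, two independent means, 1:1 allocation, 20% dropout, 140 randomised. Sidedness is not stated, so both versions are shown.

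**1. Does 118 per group follow from the inputs?** The normal approximation is n per group = 2(z_alpha + z_power)² / d².

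- Two-sided: 2 × (1.960 + 0.842)² / 0.447² = 78.6, so 79. The noncentral t calculation, which is what G*Power uses for two means, gives 80 (160 in total).
- One-sided: 2 × (1.645 + 0.842)² / 0.447² = 61.9, so 62. Noncentral t gives 63 (126 in total).

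Neither gives 118. With 118 per group, power would be 92.8% two-sided or 96.2% one-sided.

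**2. Is 118 a total mislabelled as per group?** That means 59 per group. The required totals are 160 or 126, not 118. Power at 59 per group is 67.3% two-sided or 77.9% one-sided. Fifty-nine per group has 80% power at d = 0.52 two-sided or 0.46 one-sided, not at 0.447.

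**3. Does another setting give 118?** At d = 0.447, two-sided, 90% power needs 107 per group and 95% needs 132. Alpha of 0.025 at 80% power needs 97. A Mann–Whitney efficiency correction gives 80/0.955 = 83.8, so 84. A paired test needs 42. The nearest match is two-sided alpha of 0.01, at 119 per group, which contradicts the stated 5% and the final 70 per group.

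**4. Does the dropout step work?**

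| Starting figure | N/(1 − 0.2) | N × 1.2 |
|---|---|---|
| 236 (118 per group) | 295 | 283.2 |
| 118 as a total | 147.5, so 148 | 141.6, so 142 |

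None of these is 140. The closest is 142, which uses the wrong inflation (multiplying by 1.2 instead of dividing by 0.8). In the other direction, 140 × 0.8 = 112 evaluable, or 56 per group, which is below 118 even as a total.

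**5. What power does the design have at d = 0.447?** Noncentral t, 5% level:

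| Evaluable per group | Two-sided | One-sided |
|---|---|---|
| 56 (20% lost) | 65.0% | 76.0% |
| 63 (10% lost) | about 70% | about 80% |
| 70 (none lost) | 74.7% | 83.8% |
| 80 | 80.2% | – |

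By normal approximation for 56 per group, two-sided: 0.447 × √(56/2) − 1.960 = 0.405, giving 65.7%, in line with the table.

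**6. What effect does the design detect with 80% power, two-sided?** d = 0.534 with 56 per group, and d = 0.477 with 70 per group.

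**The case against.** The contradiction itself cannot be answered, but three points bear on its size.

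*Sidedness is open.* The hypothesis is worded directionally, and a one-sided test would need 63 per group and have 83.8% power with all 70. That stands as a condition on the figures of 80 per group and 65%. It does not restore the claim: after the plan's own 20% dropout, one-sided power is still 76%. Two-sided is also the usual reading of an unqualified P < 0.05.

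*Dropout may not mean missing outcomes.* Withdrawal criteria says that withdrawn participants will still be followed for outcomes and analysed by intention to treat, and two weeks without exercise counts as withdrawal. If some of the 20% still supply outcomes, power lies between the 20%-lost and none-lost rows above: 65% to 75% two-sided, 76% to 84% one-sided. This is fair and the range should be kept in view. Two-sided, even complete follow-up falls short of 80%. One-sided, 80% is reached only if loss is about 10% or less, half of what the plan allows for.

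*The 118 is probably a labelling slip.* A total of 118 enlarged by roughly 1.2 comes close to 140, and 70 per group is consistent throughout, so conduct is unaffected. That is the likeliest origin, but 118 in total does not follow from 0.447 either, so correcting the label alone would leave the paragraph wrong.

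**Conclusion.** The paragraph is wrong as written. Two conclusions need no assumption about sidedness: 118 per group cannot become 70 per group after a dropout allowance, and 118 does not follow from the stated inputs either per group or as a total.

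The power shortfall depends on sidedness and on how many outcomes are lost. Two-sided with the planned 20% loss, power at 0.447 is 65%, so the chance of missing the target effect is about 35% where the plan allows for 20%. One-sided with the same loss, that chance is 24%. The stated 80% can be reached only by combining a one-sided test with about 10% loss or less. All figures assume a two-sample t test on a single endpoint.

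**What to change.** Rewrite the Sample size paragraph, without enrolling more:

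- Delete the figure of 118 per group.
- State that the test is two-sided and which endpoint the effect size of 0.447 refers to.
- State that 0.447 at two-sided 5% and 80% power needs 80 evaluable per group.
- State that 140 randomised with 20% dropout leaves 112 evaluable, which gives about 65% power at 0.447 (75% if nobody is lost), or 80% power at an effect of about 0.53. The 0.53 describes what this number can detect; it should not be presented as a newly justified target effect.

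Should the sponsor prefer to keep 80% power at 0.447, the matching number is 80/0.8 = 100 per group, 200 randomised. The correction does not depend on that choice.

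The cost is one paragraph, plus any other public record that repeats these figures, and a less favourable stated power. Trial status reports 16 patients recruited at the time of writing, so the correction could have been made well before results.

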### Participants

#### Inclusion criteria

Patients will have to meet the following eligibility criteria to be included in the study:
Age 45–75 yearsMeeting the diagnostic criteria of SCAD formulated by by the interventional cardiology group of the cardiovascular disease branch of the Chinese Medical Association, the Atherosclerosis and Coronary Heart Disease Group, and the Professional Committee for the Prevention and Treatment of Thrombosis of the cardiovascular physicians branch of the Chinese Medical Association [32]Heart rate > 60 beats/min [33]Living in Suzhou for at least 6 months from the start of the trialThose who are sane, rational, and able to communicate verballyThose who agree to participate and provide written informed consent

#### Exclusion criteria

Patients will be excluded from the study if:
Revascularization has been carried out or conducted in follow-upCombined arrhythmia shows on an ECGAny self-reported respiratory disorderSevere liver and kidney diseasesDiagnosed with hypothyroidism or currently taking thyroid medicationsDiagnosed with moderate or below anemia (hemoglobin [Hb] level < 9 g/dL)With any mental disorders (for example, major depressive disorder, anxiety disorder, substance use, etc.) in the past 12 monthsPregnancy and/or practicing yoga/meditation/relaxation/mindfulness on a regular basisOther reasons determined by the investigators that make participation in the clinical trial inappropriate

#### Withdrawal criteria

Participants who meet the criteria summarized below are withdrawn from the study. The individuals who are withdrawn after randomization will be followed up for outcomes. Reasons for withdrawal will be documented in follow-up records and data will be analyzed using the intention-to-treat (ITT) principle [34]:
Failed to exercise for 2 weeks in a rowFailed to have three consecutive telephone connections during the follow-up periodPatients who quit for various reasons

### Randomization

Eligible participants who will provide written consent to participate in this clinical trial will be randomly assigned to a treatment group or a control group with an allocation ratio of 1:1. Random sequencing will be generated by an independent professional statistician using the EXCEL to generate 140 random numbers. The serial numbers assigned to each patient are kept in an opaque, sealed envelope. All the participants will be asked to pick one sealed envelope and pass it onto the research study team member. The participants will be randomly assigned to two groups. Each group will have 70 individuals.

### Blinding

The research study team member who enters information about a participant’s eligibility is the only person to know the participants’ allocation until the participant has completed the entire protocol. The research team member involved in the subjective efficacy assessments is blinded to the participant’s group allocation to receive VBE or conventional treatment. Participants are similarly blinded to their own group allocation and they will be cautioned not to remark on the VBE exercises that they receive to the research study team member performing the outcome measures. Results from the outcome measures will not be revealed to the participants until after all recruitment, treatment, and assessments have been performed for all 140 participants.

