#### Intervention group

After enrollment, the intervention group was given the following measures on the basis of receiving the routine health education. Each patient in the intervention group will be assigned a health management document and have a follow-up timetable.
Development and distribution of manuals: the Chinese Biomedical Literature Database (CBM) will be searched using the Chinese search terms “health management,” “diet,” “exercise,” “heart rate,” and “blood pressure” and the Cochrane Library, JBI, and Medline will be searched using the corresponding English search terms. After two rounds of expert consultation, the health education manual for patients with SCAD will be constructed and distributed to each patient in the intervention group upon discharge.One-to-one telephone follow-up or home visit: the patient will be followed up after discharge. Follow-up time is 3 months for a total of 12 weeks (once a week in the first month and once a month after that until 3 months). Two follow-up methods will be adopted: telephone and home visit. The telephone follow-ups last about 5–10 min each. Holding time could be extended if there is any problem consultation. Home visits will be scheduled with patients in advance and will last about 30–60 min each. During the follow-up, we will address the patient’s doubts and evaluate the effectiveness of the intervention.VBE guidance: before VBE, patients should rest for 5 min and then do it in a well-ventilated room with appropriate temperature. The researchers help patients take comfortable positions (supine, repose, and standing are all acceptable, sitting is recommended), straighten their head and back, and relax their whole body. The researchers instruct patients to extend the duration of exhalation and inhalation, and to minimize the breathing rate to 6 breaths/min. Participants practice silently counting from 1001 to 1004 on the inhale phase and 1001–1006 on the exhale phase to control the breathing rhythm and slow down the frequency. Participants are also encouraged to use abdominal breathing (a bulge in the abdomen when inhaling and a depression when exhaling) to deepen breathing depth and reduce breathing rate. Practice time: the total time per day is more than 30 min [25], which can be delivered in batches, but for at least 10 min at a time and at least five times a week [12].

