Attention: The participants should breathe in and out of the nose during the whole process. The intensity of the exercise should not cause breath-holding or any physical discomfort. If discomfort occurs, participants may rest for a while and continue the exercise if no discomfort is present. For the first 3 days of the study, participants are asked to complete exercises in an outpatient classroom and the researchers will assess whether the exercises are correct or if they need to correct wrong breathing patterns.
4.Exercise log: each participant is given an exercise log and asked to record the number and time of exercise every day. These data can be used to assess intervention compliance.5.Network support: the research group will make self-breathing exercise material or video and transmit it to each participant through the network, so that participants could browse at any time.

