#### Control group

Routine education: on the first day after enrollment, researchers explain relevant knowledge of SCAD to patients, including risk factors, diet, weight control, physical exercise, blood pressure, lipid management, etc.Telephone follow-up: once per month for 3 months, each call lasting about 5–10 min, receiving telephone counseling from patients.Post-intervention: the control group will be given the same intervention measures 3 months later, and the effects of the control group will be compared before and after the intervention.

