#### Secondary outcome measure

SAS: the Zung SAS is an anxiety measure designed by William WK Zung in 1971 to quantify the level of anxiety for patients experiencing anxiety-related symptoms [28]. The SAS test is self-administered, with each response using a 4-point scale, ranging from “none of the time” to “most of the time.” There are 20 questions with 15 increasing anxiety level questions and five decreasing anxiety questions. According to SAS standard scores, the respondents are divided into four categories: no symptoms of anxiety (< 50 points); mild anxiety (50–59 points); moderate anxiety (60–69 points); and severe anxiety (≥ 70 points). The scale has been widely used in China and its validity and reliability have been verified.Metabolic profile: TC, TG, HDL-C, and LDL-C.Body composition: weight and BMI.

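### The protocol says participants are blinded and that one team member alone knows the allocation; its own procedures rule out both, so the self-rated anxiety score is unblinded

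*Protocol article*

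**What the plan says.** Study design and setting gives the label: "This is a 6-month, single-blind RCT that will be conducted in the First Affiliated Hospital of Soochow University". The Blinding section then makes three claims.

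- On the person who enters eligibility information: this person "is the only person to know the participants’ allocation", until the participant has completed the whole protocol.
- On assessment: "The research team member involved in the subjective efficacy assessments is blinded".
- On patients: "Participants are similarly blinded to their own group allocation and they will be cautioned not to remark on the VBE exercises that they receive".

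The Statistical analysis section adds that an independent statistician will analyse the data blind.

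On the anxiety outcome, the Objectives section makes exploring an effect on anxiety the second objective. The Secondary outcome measure section says "The SAS test is self-administered". Table 1 schedules the scale at screening and at week 12.

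**The concern.** This is a stated property of the design that the trial does not have, not a detail left to a fuller document. The outcome most exposed is the one that patients rate themselves. Patients who know that they are practising the tested treatment may report less anxiety because they expect to, or because they think it is hoped for. If the blinding statements pass unchanged into the results report, a reader who takes them at face value will give the anxiety comparison more credit than the design can support.

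**Working it through.** The protocol gives no figure on this point, so the check is to set the blinding statements beside the procedures.

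**Are participants blinded?**

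- *Breathing arm (Intervention group section).* "The researchers instruct patients to extend the duration of exhalation and inhalation, and to minimize the breathing rate to 6 breaths/min". Practice exceeds 30 minutes a day, at least five times a week. For the first 3 days, "participants are asked to complete exercises in an outpatient classroom and the researchers will assess whether the exercises are correct". Each patient keeps a daily log and is sent exercise material or video.
- *Control arm (Control group section).* Routine education on the first day and one call a month for 3 months. No sham breathing or attention control is described. Afterwards, "the control group will be given the same intervention measures 3 months later".
- *The blinding sentence itself.* It asks patients not to mention the breathing exercises they receive, which presupposes that they know they receive them.
- *Masking of the comparison.* Patients consent after an explanation and each picks a sealed envelope (Randomization section). Nothing describes concealing the comparison or the hypothesis from them.

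A patient in the breathing arm therefore cannot be unaware of practising the exercises, and the statement fails.

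**Does only one person know the allocation?** Researchers teach and correct the breathing. They contact the breathing arm weekly in month 1 and monthly after that, against monthly throughout for controls. They also collect the exercise logs after 2 weeks (Protocol supplementary section). These staff must know who is in the breathing arm, so this statement fails too.

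**What follows for the SAS?** The rater is the patient. Blinding the staff member who handles the questionnaire leaves the rating unblinded. Week 12 is the end of the parallel-group comparison, so it sets patients who have practised for 3 months against patients who have not been given the exercises. The unequal contact in month 1 adds to the same exposure.

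**How much could it matter? (illustration only)**

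Inputs:
- 70 per arm, from the Sample size section.
- 56 per arm = 70 × 0.8, applying the 20% dropout stated there.
- Two-sided 5% test and no true effect on anxiety (assumed).
- A mean shift of b SD caused only by knowing the allocation (assumed; the document gives no value).

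Formula: with n per arm, the noncentrality is b × √(n/2), and by normal approximation the rejection probability is Φ(b√(n/2) − 1.96) + Φ(−b√(n/2) − 1.96).

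- n = 56, b = 0.2: 0.2 × √28 = 1.06, giving about 0.18.
- n = 56, b = 0.4: 0.4 × √28 = 2.12, giving about 0.56.

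Exact t-test calculation for both arm sizes:

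| Assumed shift b (SD) | 56 per arm | 70 per arm |
|---|---|---|
| 0 | 5.0% | 5.0% |
| 0.1 | 8.2% | 9.0% |
| 0.2 | 18.2% | 21.7% |
| 0.3 | 35.0% | 42.2% |
| 0.4 | 55.5% | 65.2% |

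**The case against.** The best defence is that participants cannot be blinded in a trial of this kind, so this is a contradiction in wording that reaches mainly one secondary outcome. Much of that stands. Heart rate variability is computed automatically from the ECG and the rate-pressure product comes from an electronic monitor. Both are less exposed, though resting heart rate and blood pressure are not fully immune. It does not rescue the two blinding statements, which are untrue whatever outcome is considered.

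Several stronger readings are tempting but go beyond the document:

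- *That the plan presents the SAS as free of expectation bias.* It nowhere says so, and it states openly that the scale is self-administered. A reader could infer protection from the claim that both the assessor and the patients are blinded, but that is inference.
- *That controls know they are waiting for the exercises.* The protocol says they will be offered them after 3 months. It does not say that they are told this at enrolment, and the consent material is not shown. It is likely, not established.
- *That a confirmatory anxiety claim is at stake.* Relief of anxiety appears in the research hypothesis, but the objective is worded as exploratory and the SAS is secondary.
- *That the table estimates the trial's real false-positive rate.* The shift is assumed. The arm size is also open: 56 applies the stated dropout, while the Withdrawal criteria section says that withdrawn patients are still followed up and analysed by intention to treat, which points towards 70. In an add-on comparison with usual care, one may also argue that expectation is part of the package effect.
- *That the single-blind label is wrong.* It fits a trial in which only the assessor is blinded. It clashes only because the Blinding section extends blinding to participants.

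**Conclusion.** The concern holds as a contradiction within the protocol. The statements that participants are blinded and that one team member alone knows the allocation are both untrue under the trial's own procedures, and this conclusion needs no assumption. It follows that assessor blinding does not protect the SAS, and that its between-arm difference at week 12 is open to expectation and reporting bias. The size of that bias cannot be taken from the document. The range of about 18% to 65% rests wholly on an assumed 0.2 to 0.4 SD shift, no true effect and 56 to 70 patients per arm, and shows only that a modest shift could matter. The document does not support extending the point to a claim that the primary outcomes are invalid or that readers are told the anxiety result is bias-free.

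**What to change.** Replace the two statements in the Blinding section with wording such as: *participants and staff delivering or following up VBE are not blinded; the outcome assessor and the statistician are blinded.* Add the ECG-room staff only if the sponsor confirms that they are blinded. The Primary outcome measure section says that they complete the recordings and that the indices are computed automatically, not that they are unaware of allocation. Make clear where the label appears that single-blind refers to the outcome assessor. Report and interpret the SAS as an unblinded, exploratory patient-reported outcome.

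The cost is wording, with no change to procedures or sample size. The price is a weaker anxiety conclusion, which is the most that this design can support.
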